#### Missing values

It should be emphasized that as few patients as possible should discontinue treatment and that all patients should be followed up and also documented after discontinuation of the treatment in order to record data required according to the ITT principle. To assess the impact of up to 20% attrition, multiple imputation approaches will be taken, accounting for proxy measures and assuming specific missingness-not-at-random patterns. The details will be documented in a statistical analysis plan. Analysis of subjects essentially observed and treated per protocol is supportive.

#### Safety

Safety analyses will be performed in the safety population. Patients in the safety population will be analyzed as belonging to the treatment arm defined by treatment received (ADOPT Online or TAU; ADOPT Treatment/ADOPT Institution: THOPAS or TAU). Patients will be included in the respective treatment arm if treatment was started/if they received at least one dose of trial treatment. Patients who refuse participation in ADOPT Online/THOPAS will also be part of the safety population.

### Data monitoring

#### Data monitoring committee

A Data Monitoring Committee (DMC) has been established. The DMC comprises three experts with expertise in conducting clinical trials and specific expertise in biostatistics, psychotherapy, and child and adolescent psychiatry. Prior to the implementation of the trials, a DMC charter will be worked out, describing goals and the work plan of the board. The DMC will assess, on an annual basis, whether the execution of the study is still ethically justified and whether performance is acceptable.

#### Harms

In the framework of the study, the evaluation of tolerability/safety will be restricted to the occurrence of serious adverse events (SAEs). An SAE is defined as an event that: (1) results in the participant’s death, (2) is a suicide attempt; (3) results in hospitalization for non-suicidal self-harm; or (4) results in hospitalization for mental health problems. All serious adverse events will be reported to the independent DMC.

#### Auditing

Monitoring will be performed by the CTCC in cooperation with the ADOPT Coordination subproject. All investigators agree that the monitor is allowed to visit the center before and during the study. The pre-study monitoring visit and all other monitoring visits will be performed by the CTCC in accordance with the trial protocol, the established quality management system (SOPs), and guidelines of the International Conference on Harmonization of Good Clinical Practice (ICH-GCP). The results of the pre-study visits will be documented and reported back to the funding agency. The monitoring strategy will be specified within a study-specific monitor manual.

### Stopping rules

#### Stopping rules for an individual patient

One (or more) of the following circumstances will result in an early study termination of single subjects (these trial subjects will be rated as dropouts): (i) withdrawal of informed consent of all parents/guardians; (ii) withdrawal of assent of the patient; (iii) unwillingness to further participate in the trial; (iv) need for inpatient treatment or other reasons affecting the patient’s well-being in the case of continued trial participation; (v) need for a different kind of treatment for health reasons according to the judgment of the attending physician.

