At the main assessment points (T1-T3/T4), the primary outcome (blinded clinician-rated AD symptoms based on parent interview) and the secondary outcomes will be assessed. In ADOPT Online, information about the use of the online tool will be collected after participating parents have provided informed consent. The intermediate assessments at T1b (ADOPT Institution) and T2b (ADOPT Treatment) will only include parent- and child-report questionnaires, and no clinical interviews. During T1b/T2b, potential treatment mediators and predictors and short forms of the parent-rated AD symptoms will be assessed. In addition, the therapist in ADOPT Treatment/ADOPT Institution will complete a questionnaire to measure adherence and treatment integrity at regular intervals during the treatment.

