#### Analysis of primary endpoint

The primary (full) analysis set is derived from the ITT principle (all patients randomized with a valid baseline assessment: ADOPT Online/ADOPT Institution: T1/ADOPT Treatment: T2 and at least one follow-up measurement). The primary outcome measures “change in AD symptoms from T1 to 13 weeks post-randomization (T2)” (ADOPT Online), “change in AD symptoms from T2 to 32 weeks post-randomization (T3)” (ADOPT Treatment) and “change in AD symptoms from T1 to 32 weeks post-randomization (T2)” (ADOPT Institution) will be evaluated by an ANCOVA, with fixed effects baseline, study center, gender and treatment arm and corresponding marginal means and contrast tests (type II sums of squares). Interactions of study center and gender with treatment arm will be explored. Data from study centers with low recruitment (i.e., < 10 patients) will be pooled. The potential clustering of observations of participants by therapist or center will be investigated using multilevel modelling. Multiple imputation approaches will be taken to assess the robustness of the results. Specifically, missing values will be separately imputed by type assuming mixtures of missingness-not-at-random patterns [102]. Imputation data sets will be post-processed by multiplication with factors and addition of offsets (tipping point analysis) [103]. Proxy measures will be taken into account to ameliorate the effects of attrition.

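### Needing inpatient or different treatment ends study participation, which contradicts the rule to follow all patients after they stop treatment

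*Protocol article*

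**What the plan says.** The section *Stopping rules for an individual patient* lists five circumstances that "will result in an early study termination of single subjects (these trial subjects will be rated as dropouts"). Items (i) to (iii) concern withdrawn consent, withdrawn assent and unwillingness to go on. Item (iv) begins "need for inpatient treatment or other reasons affecting the patient" and ends with a reference to the child's well-being if participation were to continue. Item (v) is the "need for a different kind of treatment for health reasons according to the judgment of the attending physician".

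The section *Missing values* sets the rule on follow-up: "all patients should be followed up and also documented after discontinuation of the treatment in order to record data required according to the ITT principle".

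Three further statements bear on the consequences:

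- The section *Analysis of primary endpoint* derives the primary set from intention to treat, but asks for a valid baseline "and at least one follow-up measurement".
- The section *Participant timeline* says that the intermediate assessments (T1b in ADOPT Institution, T2b in ADOPT Treatment) "will only include parent- and child-report questionnaires, and no clinical interviews".
- For missing data, the article plans multiple imputation under missing-not-at-random patterns, using proxy measures: "Imputation data sets will be post-processed by multiplication with factors and addition of offsets (tipping point analysis").

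**The concern.** Stopping the study treatment and leaving the study are different events. The missing-values section separates them; the stopping rules merge them. A child whose physician decides on another treatment, and whose family is still willing to be interviewed, must be terminated under one section and followed under the other.

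A need for inpatient or different treatment is likely to be related to poor outcome. If such children leave before the endpoint visit, the arm that loses more of them looks better than it was. The primary outcome is a rating of a videotaped interview with the parent or caregiver, so it could often be obtained while the child is treated elsewhere.

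Unequal loss is plausible from the text. Treatment as usual (TAU) covers whatever psychosocial, psychotherapeutic or drug treatment is given, whereas the section *Concomitant care* bars other intensive psychotherapy in the experimental arms. The same need for another therapy may therefore pass as usual care in one arm and trigger item (v) in the other. The article does not establish that this will happen.

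Safety observation is touched as well. Under *Harms*, hospitalisation for mental health problems is a serious adverse event, yet a need for inpatient treatment ends participation.

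**Working it through.** **1. The two rules side by side.** For (i) to (iii) there is no conflict: a family that withdraws or refuses cannot be followed. For (iv), the well-being clause can justify stopping assessments for some children. For (v) there is no such clause; it is a treatment decision. So (v), and often (iv), falls under both rules.

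**2. Which data are lost.** The endpoint visit is T2 in ADOPT Online and ADOPT Institution and T3 in ADOPT Treatment. T1b and T2b hold no clinical interview, so a child terminated before the endpoint visit has no post-baseline rating on the primary scale (DADYS-PI). ADOPT Online has no assessment between T1 and T2. A child terminated there has no follow-up measurement and falls outside the primary set as defined.

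**3. Inputs from the section *Sample size*** (analysed numbers before inflation for clustering and attrition, two-sided 5%, 80% power): Online d = 0.378 with 331 and 66; Treatment d = 0.5 with 64 per arm; Institution d = 0.6 with 45 per arm. The noncentral t distribution gives 79.9%, 80.1% and 80.4%, so the planned power is reproduced.

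**4. Assumptions.** The article gives no rates for (iv) and (v). Assume 10% lost in one arm and 5% in the other before the endpoint visit, with outcomes worse by 0.5 to 1 SD than in those who remain.

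**5. Shift in d** = (difference in loss rates) × (deficit in SD):

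- (0.10 − 0.05) × 0.5 = 0.025
- (0.10 − 0.05) × 1.0 = 0.05
- equal rates and equal deficits: 0

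**6. Consequences.** Power is by noncentral t at d minus the shift (TAU loses more). Type I error is P(|Z + shift/SE| > 1.96) with SE = √(1/n₁ + 1/n₂) (experimental arm loses more, no true effect).

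| Trial | Shift as % of d | SE | Power if TAU loses more | Type I error if experimental arm loses more |
|---|---|---|---|---|
| Online | 6.6–13.2 | 0.135 | 74.3–68.0% | 5.4–6.6% |
| Treatment | 5.0–10.0 | 0.177 | 76.0–71.4% | 5.2–5.9% |
| Institution | 4.2–8.3 | 0.211 | 77.0–73.2% | 5.2–5.7% |

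These are unadjusted t-test figures.

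**7. A lower case.** At 2% against 1%, also assumed, the shift is 0.01 × (0.5 to 1) = 0.005 to 0.01. That is about 1% to 3% of d; power stays at about 78% to 80%, and type I error is at most 5.1%.

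**The case against.** The strongest reply is that the loss is not certain. The missing-values section is the specific rule on data collection, and the stopping rule might only assign a dropout status, which the planned time-to-dropout summaries need. If so, nothing is lost. This does not fit the wording, which speaks of ending the study early and is the more binding of the two (*will* in one section, *should* in the other). It is fair, though, that the harm depends on which rule the sites follow.

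Item (iv) is weaker support than (v), because its well-being clause may cover inpatient treatment too. That stands; the clear conflict is (v).

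In ADOPT Treatment and ADOPT Institution, the intermediate assessments include parent- and child-rated symptom questionnaires. A child terminated after that point has proxy data and arguably meets the follow-up condition. That also stands, so exclusion from the primary set is claimed only for ADOPT Online. The planned imputation and tipping-point analysis are real mitigation, but they model ratings that could have been observed. If they are run on the primary set as defined, they do not reach children without any follow-up.

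The assumed rates may be high: 10% for these two items compares with planned attrition from all causes of 15% (Treatment, Institution) or 20% (Online). The lower case above answers this.

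The planned baseline adjustment raises power. With an assumed baseline correlation of 0.5 (d divided by √0.75), power under the 0.05 shift is about 80%, 83% and 85% for Online, Treatment and Institution. Without the shift it would be about 90% in each, so a loss remains, and adjustment does not remove the bias.

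Finally, the article defers attrition details to an analysis plan. But no analysis plan can supply an interview that was never held.

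**Conclusion.** The concern holds. Two current rules contradict each other for consenting families under item (v), and often under item (iv). Where the stopping rule is followed before the endpoint visit, primary-outcome data are lost for a reason plausibly related to outcome.

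The expected effect is modest: a shift of 0.025 to 0.05 in d under the assumed 10% against 5% loss, zero if rates and deficits are equal, and about 0.005 to 0.01 at 2% against 1%. The direction depends on which arm loses more. The contradiction itself rests on the text alone; the size rests entirely on assumed rates and deficits. It should be fixed because the correction is simple and the data cannot be recovered later.

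**What to change.** In the section *Stopping rules for an individual patient*, state that (iv) and (v) end the study intervention only. In both arms, continue the scheduled DADYS-PI parent or caregiver interviews and the recording of serious adverse events, where consent and the child's well-being allow. Record the event and its date, and include the later ratings in the primary intention-to-treat analysis. Keep study termination for (i) to (iii) and for cases where the assessments themselves would harm the child. Clinical decisions on treatment stay with those responsible for care.

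The cost is a change of wording and some interviews that are already on the schedule. At an assumed 5% to 10% of those randomised, this means about 21 to 41 of 414 children in the ADOPT Online intervention arm and 4 to 8 of 83 in its TAU arm, 6 to 12 of 116 per arm in ADOPT Treatment, and 4 to 8 of 83 per arm in ADOPT Institution. Sample sizes do not change.

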#### Global stopping rules

A termination of the entire consortium will be executed if both ADOPT Epidemiology and ADOPT Institution fail to reach 50% of the planned sample size, despite additional recruitment strategies. The decision will be made by all principal investigators as well as the principal coordinator.

## Discussion

The ADOPT study will inform about the benefits of online self-help for parents and intensive personalized modular treatments compared to standard approaches. These effects will be related to AD symptoms, comorbid symptoms, functional impairment, and psychological well-being. The study will also inform about putative predictors, moderators and mediators of intervention effects on AD. The modular approach will have a strong impact on clinical practice, as it will help clinicians to adapt their treatment to the needs of the individual patient. For children living in OHC, especially effects on functional impairment and quality of life, but also effects on multiple placements or early discontinuation of youth welfare interventions, will be of high relevance for the individual child, but also of economic relevance for the health care and youth welfare system.

The results will have a large impact on clinical practice, as they will (1) improve assessment of the clinical condition (also in a high-risk population of children living in OHC), (2) inform about the relation of AD and clinical diagnoses of co-existing disorders and about risk and protective factors, (3) introduce personalized modular psychological transdiagnostic treatment and increase treatment effects. Since AD is an important risk factor for the development of severe mental disorders, the results should affect the health status of the pediatric target population in later periods of life. Therefore, the results of the proposed project will be highly relevant for the assessment and treatment of children with AD and comorbid conditions.

The results of the ADOPT study will inform future guidelines on the treatment of children with AD and comorbid conditions and will help to improve guidelines and to develop usable, potentially more cost-effective, individualized modular treatment in children with AD in the mental health care system and youth welfare system.

## Abbreviations

AD: Affective dysregulation
ADHD: Attention-deficit/hyperactivity disorder
ADOPT Online: Online Parent Self-Help of Affective Dysregulation and coexisting disorders
ANCOVA: Analysis of covariance
ARI: Affective Reactivity Index
BSCL: Brief Symptom Checklist
CBCL/6-18R: Child behavior checklist (parent-rated)
CBCL-DP: Child behavior checklist dysregulation profile
CBT: Cognitive behavior therapy
CD: Conduct disorder
CCNES: Coping with Children’s Negative Emotions Scale
CSQ: Client Satisfaction Questionnaire
CTCC: Clinical Trials Center Cologne
DADYS: Diagnostikum für Affektive Dysregulation bei Kindern (Diagnostic tool for affective dysregulation in children)
DADYS-CI: DADYS child interview
DADYS-PI: DADYS parent interview
DADYS-Screen: DADYS screening questionnaire
DISYPS-III: Diagnostic System for Mental Disorders in Children and Adolescents
DMC: Data Monitoring Committee
DMM: Data management manual
DRKS: Deutsches Register Klinischer Studien (German clinical trials register)
DSM-5: Diagnostic and statistical manual of mental disorders of the American Psychiatric Association, 5th edition
ERC: Emotion Regulation Checklist
FBB-ADHS: Fremdbeurteilungsbogen ADHS (rating scale for ADHD)
FBB-BIST: Fremdbeurteilungsbogen für Bindungs- und Beziehungsstörungen (rating scale for attachment and relationship disorders)
FBB-SCREEN: Fremdbeurteilungsbogen screening (rating scale for screening)
FBB-SSV: Fremdbeurteilungsbogen SSV (rating scale for oppositional defiant disorder and conduct disorder)
FBB-TBS: Fremdbeurteilungsbogen für Trauma- und Belastungsbezogene Störungen (rating scale for trauma- and stress-related disorders)
FEEL-KJ: Fragebogen zur Erhebung der Emotionsregulation bei Kindern und Jugendlichen (questionnaire for the assessment of emotion regulation)
FPNE: Fragebogen zum positiven und negativen Erziehungsverhalten (questionnaire on positive and negative parenting behavior)
ICD-10: International statistical classification of diseases and related health problems, 10th revision
ICD-11: International statistical classification of diseases and related health problems, 11th revision
ICH-GCP: International Conference on Harmonization of Good Clinical Practice
ID: Identification number
ILF-External: Structured interview for externalizing symptoms
ILF-Internal: Structured interview for internalizing symptoms
ILF-Kontakt: Structured interview for contact-related symptoms
ILF-SCREEN: Structured screening interview
IMSB: Institute of Medical Statistics and Computational Biology
ITT: Intention-to-treat
MATCH-ADTC: Modular approach to therapy for children with anxiety, depression, trauma, or conduct problems
MMRM: Mixed model for repeated measures
No AD: Children without affective dysregulation
ODD: Oppositional defiant disorder
OHC: Out-of-home care
PMT: Parent management training
PROMIS: Patient-Reported Outcomes Measurement Information System
RCI: Reliable change index
RCT: Randomized controlled trial
RDoC: National Institute of Mental Health Research Domain Criteria
REDCap: Remote data entry system provided by the Clinical Trials Center Cologne
SAE: Serious adverse event
SBB-ADHS: Selbstbeurteilungsbogen ADHS (self-rating scale for ADHD)
SBB-SSV: Selbstbeurteilungsbogen SSV (self-rating scale for oppositional defiant disorder and conduct disorder)
SCEP: School-based Coaching for Teachers of Children with Disruptive Behavior Problems
SCL-K-9: 9-item self-report short version of the Symptom Checklist
ScouT: Social Computer-assisted Training for Children with Aggressive Behavior Problems
SOP: Standard operating procedure
SSS: Social Support Scale – short version
TAU: Treatment as usual
THAV: Treatment Program for Children with Aggressive Behavior Problems
THOP: Therapieprogramm für Kinder mit hyperkinetischem und oppositionellem Problemverhalten (therapy program for the treatment of children with hyperkinetic and oppositional problem behavior)
THOPAS: Therapieprogramm zur Optimierung Affektiver Steuerung bei Kindern (Therapy for Optimizing Affective Regulation in Children)
TRF/6-18R: Teacher’s report form
VEEB: Fragebogen zum Verhalten von Eltern bei emotionalen Belastungen ihrer Kinder (Questionnaire on coping of parents with children’s emotional distress)
